## Abstract

**Background:**

Fifty percent of all stroke survivors remain with functional impairments of their upper limb. While there is a need to improve the effectiveness of rehabilitative training, so far no new training approach has proven to be clearly superior to conventional therapy. As training with rewarding feedback has been shown to improve motor learning in humans, it is hypothesized that rehabilitative arm training could be enhanced by rewarding feedback. In this paper, we propose a trial protocol investigating rewards in the form of performance feedback and monetary gains as ways to improve effectiveness of rehabilitative training.

**Methods:**

This multicentric, assessor-blinded, randomized controlled trial uses the ArmeoSenso virtual reality rehabilitation system to train 74 first-ever stroke patients (< 100 days post stroke) to lift their impaired upper limb against gravity and to improve the workspace of the paretic arm. Three sensors are attached to forearm, upper arm, and trunk to track arm movements in three-dimensional space while controlling for trunk compensation. Whole-arm movements serve as input for a therapy game. The reward group (*n* = 37) will train with performance feedback and contingent monetary reward. The control group (*n* = 37) uses the same system but without monetary reward and with reduced performance feedback. Primary outcome is the change in the hand workspace in the transversal plane. Standard clinical assessments are used as secondary outcome measures.

**Discussion:**

This randomized controlled trial will be the first to directly evaluate the effect of rewarding feedback, including monetary rewards, on the recovery process of the upper limb following stroke. This could pave the way for novel types of interventions with significantly improved treatment benefits, e.g., for conditions that impair reward processing (stroke, Parkinson’s disease).

**Trial registration:**

ClinicalTrials.gov, ID: NCT02257125. Registered on 30 September 2014.

**Electronic supplementary material:**

The online version of this article (doi:10.1186/s13063-017-2328-2) contains supplementary material, which is available to authorized users.

## Background

After stroke, 50% of survivors are left with impairments in arm function [1, 2], which is associated with reduced health-related quality of life [3]. While there is evidence for a positive correlation between therapy dose and functional recovery [4–6], a higher therapy dose is challenging to implement, as it usually leads to an increase in costs commonly not covered by health insurances. However, when dose is matched, most randomized controlled trials introducing new types of rehabilitative interventions (e.g., robot-assisted therapy [7]) failed to show a superior effect compared to standard therapy. Thus, the need for improving therapy effectiveness remains. In search for elements of effective therapy, we hypothesize that performance feedback and monetary rewards can improve effectiveness.

It has been shown that reward enhances procedural [8] and motor-skill learning [9, 10] and has a positive effect on motor adaptation [11]. Rewards mainly improve retention of motor skills and motor adaptations [9–11]. This effect was not explained by training duration (dose) as rewarded and non-rewarded groups underwent similar training schedules [8–11]. In a functional magnetic resonance imaging (fMRI) study, Widmer et al. reported that adding monetary rewards after good performance leads to better consolidation and higher ventral striatum activation than knowledge of performance alone [10]. The striatum is a key locus of reward processing [12], and its activity was shown to be increased by both intrinsic and extrinsic reward [13]. Being a brain structure that receives substantial dopaminergic input from the midbrain, ventral striatal activity can be seen as a surrogate marker for dopaminergic activity in the substantia nigra/ventral tegmental area [14]. In rodents, Hosp et al. found that dopaminergic projections from the midbrain also terminate directly in the primary motor cortex (M1) [15]. Dopamine in M1 is necessary for long-term potentiation of certain cortico-cortical connections and successful motor-skill learning [16]. As mechanisms of motor learning are also thought to play a role in motor recovery [17], rehabilitative interventions may benefit from neuroplasticity enhanced by reward.

Here, we describe a trial protocol to test the effect of enhanced feedback and reward on arm rehabilitation after stroke at matched training dose (time and intensity). We use the ArmeoSenso, a standardized virtual reality (VR)-based training system [18] that is delivered in two versions for two different study groups, one version with and one without reward and enhanced performance feedback.

## Methods

### Ethics and reporting

The study protocol follows the Consolidated Standards of Reporting Trials (CONSORT) Statement on randomized trials of non-pharmacological treatment [19] and Standard Protocol Items: Recommendations for Interventional Trials (SPIRIT; see Fig. 5 for the SPIRIT Figure and the SPIRIT Checklist in Additional file 1) guidance for protocol reporting [20]. The study is recruiting patients at three different rehabilitation clinics. The procedures and the protocol (version 4.1 of 18 August 2016) have been approved by the responsible Ethics Committees “Ethikkommission Nordwest- und Zentralschweiz,” the “Kantonale Ethikkommission Zürich” (LU2013-079 and PB_2016-01804) and the Swiss Agency for Therapeutic Products (Swissmedic: 2014-MD-0033) and conform to the guidelines of Good Clinical Practice E6 (R1). All subjects have to give written informed consent in accordance with the Declaration of Helsinki. A quality assurance audit/inspection of this study may be conducted by the competent authority or Ethical Committees, respectively. The quality assurance auditor/inspector will have access to all medical records, the investigator’s study-related files and correspondence, and the informed consent documentation that is relevant to this clinical study.

### Study design

This multicentric trial is randomized, controlled and assessor-blinded (Fig. 1). Patients are unaware of the training characteristics of the other study group.

**Fig. 1 Fig1:**
[figure not shown]
Flow diagram illustrating the trial design and sequence

### Study population

This study includes stroke patients (maximum 100 days after stroke) who meet the following criteria: minimum age of 18 years, hemiparesis of the arm due to cerebrovascular ischemia, the ability to lift the paretic arm against gravity, a minimal arm workspace of 20 cm × 20 cm in the horizontal plane, ability and willingness to participate, as well as the absence of severe aphasia (i.e., patients who are not able to follow two-stage commands), depression, dementia and hemianopia.

### Randomization

The randomization procedure was planned and set up by an independent contract research organization (Appletree CI Group, Winterthur, Switzerland). A non-consecutively increasing, pseudo-randomly generated list of subject identification numbers (IDs) was created. IDs are chronologically assigned to each new study participant, stratified by the study center. Allocation to one of the two study groups is balanced in blocks of 4. The randomization list containing the subject ID, the corresponding group allocation and a randomly generated password was sent to an independent (unblinded) study staff member (“admin”) who has set up respective patient-user computer accounts used for accessing the therapy game. The group-specific version of the game, i.e., either with or without reward, is defined by the account. The admin keeps the assignment list and is not involved in data collection.

Immediately before the first training session, each study participant has to confirm by signature to have received a sealed envelope containing a butterfly etiquette with ID and password to access the account. The patient keeps this etiquette for the entire study duration.

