### Intervention

In addition to standard therapy, both groups train for 1 h per day, 5 days a week for 3 weeks while inpatients in a participating rehabilitation hospital. Note that for study participants, standard therapy excludes additional proximal-arm training. All other therapies, however, are not affected by the study.

ArmeoSenso training is supervised by a therapist. Since 1 h of consecutive upper-limb training per day without weight support can be too demanding for some patients, deviations from this protocol are allowed to a minimum cumulative training time of 720 min.

A typical ArmeoSenso training session is described in Wittmann et al. [21]. For the present study, patients log in to their user account with their random ID and the password printed on their butterfly etiquette. The IMUs are fixed to the affected lower and upper arm and to the trunk using custom-made Velcro straps (Balgrist Tec AG, Zurich, Switzerland). The supervising therapist may help if necessary. The ArmeoSenso system then guides the patient through three calibration poses and two automated assessments (see the “Outcome measures” section) before training starts (beginning of the targeted 60-min session duration). In order to prevent physical exhaustion, the patient is visually instructed to rest for at least 4 s every 40 s. Moreover, patients are allowed to interrupt the training session if an additional break is needed. The duration of the additional breaks is added at the end of the training session. After 60 min of net training time, the automated assessments will be repeated and the patient will be asked to fill in a short motivation questionnaire (see the “Secondary outcome” section).

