Both groups train with modified versions of the ArmeoSenso “METEORS” game (see [18, 21]). Although the two versions differ markedly in terms of their appearance, they share the underlying game mechanics. That is, in both a virtual “hand” which matches the movement of the subject’s real hand is used to catch objects that drop downwards from the top of the screen. The targets are placed within, or at the border of, the patient's virtual 3D workspace, which is continuously estimated and updated using a voxel-based model [18]. The time to complete a round in the METEORS game is T_max = 150 s (excluding rest). If, during these 150 s, less than five targets were missed, the round is won and the difficulty increases by up to three levels, depending on the number of targets that hit the ground. Difficulty is adapted dynamically by changing (1) the average target speed of falling, (2) the target spawn interval and (3) the number of simultaneously spawned targets (one to a maximum of seven). It increases in this order (i, ii, iii, i, …). Conversely, difficulty decreases in reverse order if more than four targets were missed and the round is lost after a certain time (T_loss). In that case, the difficulty decrease is calculated by rounding $$ \frac{T\_\mathit{\max}}{T\_ loss} $$ to the closest integer, but with a maximum of four difficulty levels.

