### Sample size

The sample size is estimated to detect a between-group difference of 4.8 voxels in the workspace difference from beginning to end of training, based on the improvement in arm workspace from pilot results (unpublished) and an estimated group difference of 20%. This assumes a two-sided alpha level at .05 and a power of 80%. For an effect with a standard deviation of seven voxels, 35 subjects per group yields 80% power to detect the true alternative. We will randomize 37 subjects in each group, based on our observed attrition rate of 5% in a previous interventional trial [21]. This calculation was performed using G*Power 3.1 [24, 25].

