### Trial status

The trial is currently recruiting patients. At the time of submission, 16 stroke patients have been enrolled.

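### One fixed block size of 4 per centre, disclosed during recruitment and paired with visibly different games, lets a fully informed observer deduce up to a third of allocations

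*Protocol article*

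**What the plan says.** Under Randomization, the protocol article says "IDs are chronologically assigned to each new study participant, stratified by the study center", and then "Allocation to one of the two study groups is balanced in blocks of 4". No variation in block size is mentioned. The natural reading is a separate 2:2 blocked sequence in each centre, and under Ethics and reporting there are three: "The study is recruiting patients at three different rehabilitation clinics".

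The same section describes safeguards for the list. An independent contract research organisation generated it, the IDs are not consecutive, an administrator outside data collection holds it, and each patient receives login details in a sealed envelope just before the first session.

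Under Intervention, "ArmeoSenso training is supervised by a therapist", and "Although the two versions differ markedly in terms of their appearance, they share the underlying game mechanics". Outcome measures describes the assessors as blinded. Study design adds that patients do not know what the other group's training looks like. Therapists are not said to be blinded.

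On timing, Trial status reports: "The trial is currently recruiting patients. At the time of submission, 16 stroke patients have been enrolled". The planned total is 74: "We will randomize 37 subjects in each group, based on our observed attrition rate of 5% in a previous interventional trial".

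**The concern.** The safeguards hide the list, but they do not hide allocations already made. Once a patient starts training, anyone watching can tell a game with scores and money from a plain one with neither. With a constant, disclosed block size, the past allocations at a centre can fix the next one.

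If that knowledge reached someone who influences enrolment, patients with better prospects could be timed or steered towards one arm, even without intent. Study population leaves some room for this: part of eligibility is ability and willingness to take part, and the entry window runs to 100 days after stroke. Blinded assessors and an automated primary outcome give no protection against selection at entry, and such bias is hard to repair in the analysis.

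**Working it through.** The plan gives no figure for predictability. Its sample size is not in question: a difference of 4.8 voxels, SD 7, two-sided 5% gives 80.7% power at 35 per group by the noncentral t test (79.6% at 34), and 35/0.95 = 36.8, so 37 per group.

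**Inputs.** Block size 4, allocation 1:1, three centres, 74 planned, 16 enrolled at submission, so 74 − 16 = 58 remaining.

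**Certain allocations in a 2:2 block (six equally likely orders).**
- Positions 1 and 2: never determined.
- Position 3: determined if the first two match, probability 1/3.
- Position 4: always determined.
- Sum: 0 + 0 + 1/3 + 1 = 4/3 per block; share (4/3)/4 = 8/24 = 33.3%.

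**Best-guess hit rate.** By position: 1/2, 2/3, (1/3 × 1) + (2/3 × 1/2) = 2/3, and 1. The mean is (1/2 + 2/3 + 2/3 + 1)/4 = 17/24 = 70.8%, against 50% by chance.

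**Remaining patients.** 58 × 1/3 = 19.3 expected. The article does not give enrolment by centre. Over all possible splits of the 16 and the 74 across three centres, the expected number runs from 17.3 to 20.7 (30% to 36%). If the blocks formed one sequence across centres, it would be 14 complete blocks × 4/3 = 18.7 (32%), but the observer would need to know allocations everywhere.

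**Delay before an arm becomes visible.**
- Latest patient's arm not yet seen: only position 4 can be determined, and only if the first two match, so 1/3 × 1/4 = 8.3%, or 58 × 0.083 = 4.8 patients.
- Last two not yet seen: 0%.

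**Illustration of possible bias (the steering effect is an assumption).** Suppose every certain slot were used to shift expected change by d voxels in opposite directions by arm. The group difference would be biased by 2 × (certain slots)/74 × d. Take d as 0.25 to 0.5 of the planning SD, that is 1.75 to 3.5 voxels.
- 19.3 slots: 0.52d = 0.9 to 1.8 voxels, or 19% to 38% of the 4.8-voxel target.
- 4.8 slots: 0.13d = 0.2 to 0.5 voxels.
- No certain slots: zero from this source.

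**Effect of other block schemes** (mixed sizes simulated with 24 or 25 patients per centre, the observer knowing the set of sizes but not their order):

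| Scheme | Certain | Best guess correct |
|---|---|---|
| Fixed 4 | 33% | 70.8% |
| Fixed 6 | 25% | 68.3% |
| Random 4, 6 | about 6% | about 68–69% |
| Random 2, 4, 6 | about 4% | about 69–70% |

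**The case against.** One third is a ceiling. It needs an observer who knows every previous allocation at the centre in order, knows where the blocks start, and has already seen the latest patient's game. This stands, and it is why the range down to 8.3% and 0% belongs with the figure. Accrual by centre is not given. If recruitment began soon after registration on 30 September 2014 (an assumption), 16 patients across three centres by a submission that cites a protocol version of 18 August 2016 is slow, and the upper end is the likelier one.

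A reader might infer that concealment has failed, or that therapists enrol patients or pass on what they see. No statement in the article supports this. Who screens and enrols is detail that a condensed article may leave to the full protocol, so its absence is not held against the plan. That therapists see the game is itself an inference from supervision and the visual difference.

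A reader might also infer that early recovery is the main source of variation in the outcome. The Discussion says only that most recovery falls in this period and that both groups are expected to improve.

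Two further objections stand in part. Publication follows submission, so patients enrolled in between were not exposed through the article, and nothing says whether sites knew the block size before. Most entry criteria are specific, which limits steering without removing discretion.

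**Conclusion.** The design weakness is real and follows from what the article states: a single block size of 4, natural reading within centre, disclosed during recruitment, with arms that can be told apart on sight. Up to one third of allocations can be deduced with certainty by a fully informed observer, which is about 19 of the 58 outstanding at submission. That number is an expectation under ideal knowledge, not a count of allocations known to anyone.

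The conclusion is limited to a potential for selection bias. Its actual size depends on three things that the article does not give: how quickly patients follow one another at a centre, whether those who influence enrolment learn the previous arms, and whether they would act on them. The bias figures above are illustrations of an upper-end case. The sample size is unaffected. The change is worth making because 58 of 74 patients (78%) were still to be enrolled at submission.

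**What to change.** Ask the independent provider to re-issue the unused part of the list with randomly varying block sizes within centre, for example 4 and 6, or 2, 4 and 6, and withhold the sizes from sites until recruitment ends.

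The gain is in certainty: deducible allocations fall from 33% to about 6% (4 and 6) or 4% (2, 4 and 6). The best-guess rate barely moves, from 70.8% to about 68–69% or 69–70% respectively, so the change should not be presented as making allocation unpredictable.

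The costs are a new list, set-up of the matching user accounts by the administrator, possibly an amendment because the protocol has ethics and Swissmedic approval, and a slightly larger possible imbalance within a centre at the end of recruitment.

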### ArmeoSenso training system

The arm rehabilitation system combines motion capturing via wearable inertial measurement units (IMUs) in combination with a therapy game, running on a touch screen computer (Inspiron 2330, Dell Inc., Round Rock, TX, USA) (Fig. 2a). Three wireless IMUs (MotionPod 3, Movea SA, Grenoble, France) are fixed to the functionally impaired lower and upper arm as well as the trunk [18, 21].

**Fig. 2 Fig2:**
[figure not shown]
**a** Healthy subject using the ArmeoSenso training system. **b** Arm workspace assessment: *gray cubic* voxels arranged in the transverse plane reflecting 10 cm × 10 cm active workspace relative to the patient’s trunk

In contrast to robot-based VR therapy systems, this sensor-based approach does not offer any weight support for the impaired arm. The ArmeoSenso system specifically requires the patient to lift the arm against gravity and to increase hand workspace in three-dimensional (3D) space. The system was validated in a home feasibility trial with stroke patients [21]. For the present study, the ArmeoSenso system includes two automated functional assessments, one consisting of a pointing task with nine targets arranged in two semicircles in the transversal plane. The second assessment measures the hand workspace of the trained limb (see the “Primary outcome” section). While identical assessments are performed in both training groups, the system includes a specific version of a therapy game for each of the two training groups: (A) a rewarding version including monetary rewards, knowledge of performance feedback and graphical special effects (Fig. 3a) and (B) a non-rewarding version lacking these motivators (Fig. 3b). A more detailed description follows.

**Fig. 3 Fig3:**
[figure not shown]
**a** ArmeoSenso-Reward: “METEORS” therapy game. The hand of the virtual arm is used to catch the falling meteors before they crash onto the planet. If caught, the meteor explodes and a score appears. If missed, the planet gets damaged (note the impact crater). The current score (= PUNKTE) is displayed on the upper left (*white font color*) and compared to the patient’ all-time record (= REKORD; *red font color*, *upper left*). The *green* bar on the *upper right* indicates resting time. If completely black, the patient has to rest for 4 s before new meteors are spawned. During rest, the bar fills with green. The *yellow bar* on the *left* indicates how much playtime is left in the ongoing round (maximum 150 s). **b** Control game. The virtual hand is a *green decagon* that can be used to touch the pill-shaped, single-colored targets dropping in from the top of the screen, which then disappear with a delay of 1 s without producing a score. The *green bar* on the upper *right* fills up whenever the patient assumes the resting position

### Intervention

In addition to standard therapy, both groups train for 1 h per day, 5 days a week for 3 weeks while inpatients in a participating rehabilitation hospital. Note that for study participants, standard therapy excludes additional proximal-arm training. All other therapies, however, are not affected by the study.

ArmeoSenso training is supervised by a therapist. Since 1 h of consecutive upper-limb training per day without weight support can be too demanding for some patients, deviations from this protocol are allowed to a minimum cumulative training time of 720 min.

A typical ArmeoSenso training session is described in Wittmann et al. [21]. For the present study, patients log in to their user account with their random ID and the password printed on their butterfly etiquette. The IMUs are fixed to the affected lower and upper arm and to the trunk using custom-made Velcro straps (Balgrist Tec AG, Zurich, Switzerland). The supervising therapist may help if necessary. The ArmeoSenso system then guides the patient through three calibration poses and two automated assessments (see the “Outcome measures” section) before training starts (beginning of the targeted 60-min session duration). In order to prevent physical exhaustion, the patient is visually instructed to rest for at least 4 s every 40 s. Moreover, patients are allowed to interrupt the training session if an additional break is needed. The duration of the additional breaks is added at the end of the training session. After 60 min of net training time, the automated assessments will be repeated and the patient will be asked to fill in a short motivation questionnaire (see the “Secondary outcome” section).

Both groups train with modified versions of the ArmeoSenso “METEORS” game (see [18, 21]). Although the two versions differ markedly in terms of their appearance, they share the underlying game mechanics. That is, in both a virtual “hand” which matches the movement of the subject’s real hand is used to catch objects that drop downwards from the top of the screen. The targets are placed within, or at the border of, the patient's virtual 3D workspace, which is continuously estimated and updated using a voxel-based model [18]. The time to complete a round in the METEORS game is T_max = 150 s (excluding rest). If, during these 150 s, less than five targets were missed, the round is won and the difficulty increases by up to three levels, depending on the number of targets that hit the ground. Difficulty is adapted dynamically by changing (1) the average target speed of falling, (2) the target spawn interval and (3) the number of simultaneously spawned targets (one to a maximum of seven). It increases in this order (i, ii, iii, i, …). Conversely, difficulty decreases in reverse order if more than four targets were missed and the round is lost after a certain time (T_loss). In that case, the difficulty decrease is calculated by rounding $$ \frac{T\_\mathit{\max}}{T\_ loss} $$ to the closest integer, but with a maximum of four difficulty levels.

